#### Soil

A metal spatula will be used to collect a single soil sample (5 – 10mL) in a 50mL conical tube. This will be collected from all non-cement floors from the kitchen, the sleeping area, the living area, and just outside the primary entrance. Soil samples are not collected if the homes have cement floors. Samples will be refrigerated for up to 18 hours before processing. DNA will be extracted from soil samples using the DNeasy Power Soil Pro Kit (Qiagen, Hilden Germany) per manufacturer instructions.

#### Milk and maize porridge samples

Milk and maize porridge samples will be obtained if they are available in the home on the day of sampling. The caregiver will be asked to serve the milk and porridge or liquid in the way she would give it to the child that day. Up to 5 mL of milk and 10 mL of maize porridge will be collected from the caregiver in a 50mL conical tube. Both milk and maize porridge samples will be placed in a cooler bag with ice packs for transport to the lab. Porridge samples will be homogenized using a bag mixer before DNA extraction. Samples will be refrigerated for up to 18 hours before processing. DNA will be extracted from milk and porridge samples using the QIAamp DNA Mini Kit (Macherey-Nagel, Düren, Germany) per manufacturer instructions.

#### Drinking water

One liter of drinking water will be collected from the household drinking water container and maintained at 4 °C until delivery to the laboratory for concentration and nucleic acid extraction. The water will then be filtered through (up to 3) Argonide filter(s) using a vacuum manifold. The pathogens captured on the filters will then be eluted from the filters using a 1x PBS/0.05 M glycine/ 1% sodium polyphosphate solution, and the eluent will be further concentrated using centrifugal Amicon filters. The final concentrate (approximately 200uL) will be stored at −80°C until TNA extraction, using the QIAmp Fast DNA Stool mini kit (Qiagen, Hilden Germany).

#### Flies

The day prior to each visit for environmental sampling, a fly strip will be distributed to the participants to set up in the home’s cooking area to capture flies over a 24-hour period. At the end of this period, the total number of flies on the tape will be enumerated and field workers will place up to 10 flies into a collection tube and store at −80°C until further processing. The DNA will be extracted from crushed flies using the NucleoSpin^®^ DNA Insect Mini Kit (Macherey-Nagel, Düren, Germany) following manufacturer instructions.

#### Dried Blood Spots

Dried blood spot (DBS) samples will be collected from the index child at home visits by trained study staff via a finger or heel stick to capture 300 μl of whole blood on filter paper in accordance with WHO protocols ^[20]^. DBS will be collected at enrollment and twice during follow-up time points at 6 and 12 months, and within +/− 7 days collection window. DBS will be transferred onto a card, air dried, and kept at room temperature away from direct sunlight until serologic studies are performed ^[21,22]^.

### Detection of *Campylobacter* and *Shigella* by multiplex qPCR

All nucleic acid extracted from human and fecal and from environmental samples will be stored at −80 °C until testing. Testing will consist of a TaqMan-based multiplex qPCR assays to detect *Campylobacter* spp. using species-specific primers and probes targeting the atpA gene^[23]^ and *Shigella* targeting the ipaH gene^[24]^. The assays will be performed on a ViiA7 machine (Thermo Fisher Scientific, Waltham, MA) at an initial heat activation step of 95 °C for 20 min, 40 cycles of two-step PCR including denaturation at 95 °C for 3 seconds, and annealing and extension at 60 °C for 45 seconds.

### Serologic testing

DBS will be tested for IgG against conserved *Shigella* (IpaB) and *Campylobacter jejuni* (p18 and p39) proteins using multiplex bead assays ^[25,26]^. Beads will be stored at 4°C until use, when they will be combined into a multiplex solution and mixed with a concentration of roughly 1000 beads per set per microplate well. DBS will be eluted and added to the solution in each well. The plate will be incubated for 1 hour, after which PE-labeled anti-human IgG will be added and incubated for 1 hour. The plate will be washed with PBS containing 0.05% Tween 20, and then the mean fluorescent intensity will be measured using a Luminex instrument (Luminex Corporation, Austin, Texas, United States).

### Data analysis

The goals of the analysis are to identify possible sources and transmission pathways for *Shigella* and *Campylobacter* using two complementary approaches of statistical and mathematical modeling, whereby the former helps inform the latter. Specifically, we will generate measures of disease incidence, pathway-specific relative risks, environmental contact rates, and duration of pathogen shedding, all of which will inform and parameterize the transmission models. We will then develop complementary transmission models to characterize the relative importance of person-to-person and environmental transmission.

To identify potential sources for infections in index children, we will compare the prevalence of the target pathogen in environmental and familial samples between infected and uninfected index children. We will evaluate possible sources for *Shigella* as well as for *Campylobacter* species identified in at least 5% of stool samples from index children. Source types will be categorized into six pathways with their respective sample types: people (samples: caregiver and sibling stools), animals (animal feces), flies, food, water, and soil. Pathogen burden in each pathway will be characterized as the total qPCR Cq-derived quantity of species-specific pathogen detected in samples from that pathway. The duration of convalescent shedding will be estimated based on the median time from the onset of symptoms to the final positive convalescent stool performed on all qPCR-positive convalescent stool samples.

We will estimate the associations between pathogen quantity in an environmental pathway and infection in the index child using log-binomial regression with generalized estimating equations to account for correlation between samples from the same child over time. We will adjust for age and month of the year given the expected seasonality of exposure. Using the estimated relative risks for each transmission pathway, we will estimate attributable fractions (AF), where AF = 1 – 1/RR and RR is the relative risk for each pathway. We have previously used the attributable fraction methodology to attribute diarrhea etiologies^[18,27]^, a metric that accounts for both the prevalence of detection in a given pathway as well as the strength of association with infection and will provide a rank ordering of the relative importance of each pathway. The estimated relative risks will be used in the transmission models as described below.

The goal of the infection transmission modeling is to understand where the transmission of different enteric pathogens falls on the continuum from primarily person-to-person to primarily environment-to-person transmission, using *Shigella* and *Campylobacter* as model organisms. Our infectious disease transmission modeling approach will consist of two complementary frameworks. First, we will develop an individually based household dynamic transmission model to capture the PCR-confirmed incidence of clinical and subclinical *Shigella* and *Campylobacter* infections observed in this study. Prevalence and duration of shedding in convalescent stools will help to parameterize two model parameters: shedding rate and a factor converting shedding from humans into increases in environmental contamination. Second, we will use a compartmental model framework to develop an endemic transmission model of the cohort. We will incorporate the prevalence of collected household characteristics, environmental contacts and measured environmental exposures (water, food, flies, etc.). Finally, relative risks estimated from the associations between detections in environmental and familial samples and infections in the index child will provide informative priors for parameters that characterize the importance of person-to-person and environmental transmission.

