**Methods and analysis::**

This longitudinal cohort study will enroll 100 index infants as well as their families in Haydom, Tanzania. Families will be followed for one year, with collection of stool samples monthly and during incident diarrhea from all household members. Additionally, we will sample from the index child’s environment, including domestic animal stools, drinking water, milk, porridge, flies, and soil. All samples will undergo nucleic acid extraction and quantitative PCR for *Campylobacter* and *Shigella*. Serial serologic tests will also be performed to identify seroconversion to these pathogens. Associations between pathogen detection from the environment and household members and detection in index children will be estimated, and the temporal patterning of infection cases will be analyzed using transmission models.

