### Study design and recruitment

This longitudinal cohort study will recruit index children under one year of age as well as their household members, with enrollment occurring over approximately one year and all households followed for 12 months. The index child and all family members who sleep at the house on an average of 4 or more nights per week will be included in the study. Inclusion criteria are 1) the index child must be living in the home, defined by sleeping at the home on average at least 6 nights per week; 2) the family is not planning to move from the study area in next year; and 3) the index child must be below 1 year of age at a time of enrollment and in the current eligible enrollment age stratum (see enrollment below). They will be excluded from the study if 1) the household already has a child enrolled in the study; 2) the index child has been identified to have a developmental abnormality or congenital disease; 3) maternal age is < 18 years; or 4) the index child routinely receives care outside of the home during the day.

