#### Human stools

Stool samples will be collected upon enrollment, monthly thereafter, and at the time of diarrhea among the index children or any enrolled household member. To characterize duration of pathogen carriage, stool samples from any individual with study-defined diarrhea will continue to be collected approximately twice-weekly for 4 weeks from illness onset, with a collection window of 48 hours. Each participant will collect and provide 5 g or 5 mL of stool sample. All stool samples will be collected within 6 hours of passage and will be transported on ice followed by storage in the lab at −80 °C until TNA extraction. TNA will be extracted using a 200 mg stool aliquot using the QIAamp Fast DNA Stool Mini Kit (Qiagen, Hilden Germany) per manufacturer instructions.

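### The people pathway is limited to caregiver and sibling stools although all enrolled household members are sampled and tested, so the person-to-person exposure is incomplete and its RR may be biased in a direction the protocol cannot show

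*Protocol article*

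**What the plan says.** Enrollment is wide. Under Study design and recruitment, the index child and "all family members who sleep at the house on an average of 4 or more nights per week will be included". Collection follows enrollment: the Abstract (Methods and analysis) describes a one-year follow-up "with collection of stool samples monthly and during incident diarrhea from all household members", and Human stools repeats that samples are taken at enrollment, monthly and "at the time of diarrhea among the index children or any enrolled household member". Testing is equally wide: "All samples will undergo nucleic acid extraction and quantitative PCR" (Abstract).

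The exposure definition is narrower. Data analysis sorts sources into six pathways, and the human one is "people (samples: caregiver and sibling stools". The exposure measure is then fixed: "Pathogen burden in each pathway will be characterized as the total qPCR Cq-derived quantity of species-specific pathogen detected in samples from that pathway". The same section opens the analysis in wider terms, stating that it will "compare the prevalence of the target pathogen in environmental and familial samples between infected and uninfected index children". The Abstract likewise announces associations with detection in household members, and the transmission-modeling text again refers to familial samples. No reason is given for the narrower definition.

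**The concern.** An enrolled resident who is neither a caregiver nor a sibling gives stool that is tested but has no place in any of the six pathways. At a visit where only that person is positive, the people pathway records no pathogen. An infection acquired from that person cannot be credited to human contact.

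The people RR has three uses: it is converted to an AF by AF = 1 – 1/RR, it places people in the rank order of pathways, and it supplies an informative prior for the person-to-person parameter of the transmission models. The study aims to place each pathogen between person-to-person and environment-to-person transmission, so the content of the people pathway matters to its main conclusion.

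**Working it through.** **Side by side.** Enrolled: all family members above the sleeping threshold. Sampled: all of them. Tested: all samples. Named in the comparison: household members (Abstract), familial samples (Data analysis). Used in the people exposure: caregivers and siblings. The last set is narrower than each of the others, and nothing assigns the remainder.

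**The plan's own figure.** Sample size and power calculation gives 1500 samples from 100 children (15 per child), ICC 0.05, 10% exposed, 20% infected, two-sided alpha 0.05, 80% power and detectable RR 1.76.
- Design effect: 1 + (15 – 1) × 0.05 = 1.70, as stated.
- Effective sample: 1500/1.7 = 882, of which 88 exposed and 794 unexposed.
- Risks at RR 1.76: p0 = 0.20/(0.9 + 0.1 × 1.76) = 0.186; p1 = 0.327.
- The two-proportion formula with continuity correction gives power 81.8% and detectable RR 1.74. Without correction, the pooled version gives 1.70 and the unpooled version 1.79.

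The stated 1.76 is reproduced closely. It does not depend on who counts as people; it is used below only as a reference value.

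**Illustration 1: any-positive exposure.** Assumptions, none of them from the document for household stools: each member is positive with probability p, independently; all members are equally infectious; m residents are excluded; the true RR for any positive member is 1.76. The protocol's 10% refers to environmental samples and is borrowed here for p. Among visits coded unexposed, the share truly exposed is c = 1 – (1 – p)^m, and the observed RR is 1.76/(1 + 0.76c).

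| m | p | c | observed RR | AF |
|---|---|---|---|---|
| 0 | any | 0 | 1.76 | 0.43 |
| 1 | 5% | 0.05 | 1.70 | 0.41 |
| 1 | 10% | 0.10 | 1.64 | 0.39 |
| 2 | 10% | 0.19 | 1.54 | 0.35 |
| 4 | 10% | 0.34 | 1.40 | 0.28 |
| 4 | 20% | 0.59 | 1.22 | 0.18 |

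With three included and two excluded members at 10%, the share of truly exposed visits coded unexposed is (0.410 – 0.271)/0.410 = 34%.

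**Illustration 2: risk multiplies with each positive member.** Three included and two excluded members, each 10% positive; RR 1.76 per positive included member and R per positive excluded member.
- Independent positivity, restricted any-positive RR: (1.076³ – 0.729)/0.271 = (1.246 – 0.729)/0.271 = 1.91, whatever R is.
- Independent positivity, all-member RR: (1.246 × (0.9 + 0.1R)² – 0.590)/0.410. This is 1.60 for R = 1.0, 1.91 for R = 1.5 and 2.08 for R = 1.76.
- Correlated positivity, by simulation (latent normal correlation, baseline risk 12%, risk capped at 1). At correlation 0.3, restricted against all-member is about 2.1 against 1.8 for R = 1.0, and about 2.5 for both at R = 1.76. At correlation 0.5 and R = 1.76, it is about 3.1 against 3.0.

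So the restricted RR can be lower than, equal to or higher than the all-member RR, depending on inputs that the document does not contain.

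**The case against.** A reader might infer that the restriction certainly attenuates the people RR and tilts the comparison toward the environment. The document does not support this. Attenuation as in Illustration 1 needs other residents to be about as infectious to the infant as caregivers and siblings, and positivity to be unrelated within households. Illustration 2 shows the result changing when either condition fails. Limiting the pathway to likely close contacts can be a deliberate and defensible choice, and pooling everyone could dilute the RR.

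Further points stand:
- The planned exposure is a total quantity, not any-positive, so 1.64, 1.54 and 34% illustrate a simpler analysis than the one planned.
- Household composition and positivity by member are not given. Where no other relatives live in the home, there is no effect.
- Caregiver is not defined. The behavioral observation section speaks of a primary caregiver, so the plain term may cover more than one adult, perhaps including fathers.
- Other pathways are also incompletely measured: up to five animal types, no soil from cement floors, up to 10 flies. These limit what is collected rather than the use of tested samples, but they prevent any claim about net bias.
- The individually based household model is not stated to be limited to caregivers and siblings. It would be wrong to conclude that other residents' stools are discarded from the whole study.

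It can also be said that the parenthesis is shorthand in a condensed article. That does not remove the point: the article states a rule for the pathway, and the rule disagrees with its own wider descriptions of the same comparison.

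**Conclusion.** The point holds as an inconsistency with consequences. As written, tested stools of enrolled residents who are neither caregivers nor siblings enter no pathway, and the people RR, its AF and rank, and the person-to-person prior rest on an incomplete human exposure. The RR may be biased; neither direction nor size can be established from the document. Under the assumptions of Illustration 1, an RR of 1.76 would be seen at about 1.2 to 1.7 when one to four residents are excluded. Under weaker contact or clustered positivity it would be unchanged or higher. The finding concerns the regression and what is derived from it, not the stated power or the structure of the transmission models. It should be settled before analysis.

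**What to change.** Define the people pathway as stools of all enrolled household members other than the index child. Report caregiver, sibling and other-resident sub-pathways separately; combining the first two retains the present estimate for readers who prefer close contacts. State who counts as a caregiver, and use one term for this set of samples throughout.

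Because burden is a total over the samples in a pathway, it rises with the number of people sampled. Include the number of members sampled as a covariate, or use a mean log quantity, so that the measure does not merely reflect household size.

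The cost is a few lines of analysis text and slightly more analysis; the samples are already due to be collected and tested. The downside is possible dilution of the all-member RR if other residents transmit little, which the sub-pathway results would show.

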### Sample size and power calculation

Assuming that the source analyses are focused on transmission to the index children, and after accounting for the anticipated accrual goal and drop-out rate, a total of 1500 samples from 100 children (13 non-diarrheal and 2 diarrheal stools per index child on average from recent HDSS data) will be included in the analysis. We assumed a design effect of 1.7 to account for correlation between samples from same child, based on the intraclass correlation coefficient of (ICC) 0.05 for *Shigella* and *Campylobacter* detections within samples from the same child in the MAL-ED study^[2]^. We assume the design effect will be similar across *Shigella* and individual *Campylobacter* species. Assuming that 10% of each type of environmental sample tests positive for the target pathogen and the overall prevalence of pathogen infection is 20%, we would have 80% power to detect a risk ratio of 1.76 for each pathogen species and environmental pathway in a two-sided test with alpha=0.05. The minimum detectable risk ratio at 80% power varies by the proportion of environmental samples that test positive for the pathogen and by alternative assumptions for the design effect (Figure 1). Over a range of plausible design effects and pathogen prevalence in varied environmental sample types, we will have power to detect risk ratios that will identify the most important transmission pathways for *Shigella* and the most prevalent individual *Campylobacter* species.

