### Enrollment and follow up

To ensure balance of enrolled ages over seasons of the year, enrollment will be stratified by index child age in 3-month strata (0 – 2 months, 3 – 5 months, 6 – 8 months, and 9 – 11 months). Within each 2-week period, one household with a child in each age group will be enrolled. All enrolled index children and their families will be followed for one year from enrollment with twice-weekly visits to identify diarrhea, fever, and antibiotic use (Figure 2). Household stool and environmental samples will be collected monthly, with additional sampling during and after episodes of diarrhea. Diarrhea will be defined by self- or caregiver-report of three or more loose or watery stools in 24 hours or stool with visible blood.

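### Shedding duration is timed from symptom onset to the last positive stool after diarrhea of any cause, so infections acquired after onset count as prolonged shedding

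*Protocol article*

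**What the plan says.** Three parts of the protocol article bear on this point.

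- **What starts the series.** Under Enrollment and follow up, the case definition uses symptoms only: "Diarrhea will be defined by self- or caregiver-report of three or more loose or watery stools in 24 hours or stool with visible blood". Under Human stools, "stool samples from any individual with study-defined diarrhea will continue to be collected approximately twice-weekly for 4 weeks from illness onset". No pathogen result is needed to enter the series. A stool is also taken "at the time of diarrhea among the index children or any enrolled household member", so a diarrheal stool is planned for each episode.
- **How duration is estimated.** Data analysis gives the "median time from the onset of symptoms to the final positive convalescent stool performed on all qPCR-positive convalescent stool samples". This fixes the start of the clock (symptom onset), its end (the last positive) and the set of stools used (all positive ones). It places no condition on the diarrheal stool and has no rule for a positive that follows negatives.
- **How the estimate is used.** The transmission-modeling part of Data analysis says: "Prevalence and duration of shedding in convalescent stools will help to parameterize two model parameters". These are the shedding rate and the factor that turns human shedding into environmental contamination.

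**The concern.** The estimator is meant to measure how long a person keeps shedding the pathogen after the illness it caused. The series it is applied to follows diarrhea of any cause, in a setting the article describes as high-burden. Two kinds of episode then enter with the wrong duration:

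1. The diarrhea had another cause, the diarrheal stool was negative, and the pathogen was acquired later in the four weeks. The episode is counted as shedding since onset.
2. The diarrheal stool was positive, the person cleared, and a new infection followed within the window. The episode is timed to the last positive, across the gap.

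Both errors lengthen the estimate. At stake is an input that helps set two parameters of the transmission models.

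**Working it through.** The article states no shedding duration, so there is no figure to reproduce. The check is the literal rule plus an illustration of its possible size.

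**Literal rule.** Diarrheal stool negative, first and only positive on day 24: duration = 24 − 0 = 24 days, although shedding began no earlier than the preceding negative stool.

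**Illustrative model.** Each person is either carrying or not carrying the pathogen, and qPCR detects carriage perfectly.
- From the article: about two stools a week for 4 weeks, taken as 8 stools 3.5 days apart; 20% prevalence (the sample-size section's assumption).
- Assumed: mean carriage D of 7, 14 or 28 days; prevalence p of 2% and 5% as alternatives; share a of diarrheal episodes caused by the pathogen, 0 to 40%.
- Clearance rate μ = 1/D. Acquisition rate λ = p/[(1−p)D], so that equilibrium prevalence is p. r = λ + μ.
- Per 3.5-day step: P(negative → positive) = p(1 − e^(−3.5r)); P(positive → positive) = p + (1−p)e^(−3.5r).
- P(diarrheal stool positive): q = a + (1−a)p.

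**One case by hand** (p = 0.20, D = 7, a = 0, so q = 0.20):
- r = 0.0357 + 0.1429 = 0.1786; e^(−0.625) = 0.535.
- P(neg → pos) = 0.2 × 0.465 = 0.093; P(pos → pos) = 0.2 + 0.8 × 0.535 = 0.628.
- P(any positive among 8 | negative at onset) = 1 − 0.907^8 = 0.542.
- P(any positive among 8 | positive at onset) = 1 − 0.372 × 0.907^7 = 0.812.
- Share of contributing episodes with a negative diarrheal stool = 0.8 × 0.542 / (0.8 × 0.542 + 0.2 × 0.812) = 0.434/0.596 = 73%.

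**Median duration in days**, from enumerating all sequences of 8 stools. The reference column is the same estimator with no new acquisitions.

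| D | p | a | Negative at onset | As written | Diarrheal stool positive required | Plus two-negatives rule | Reference | As written / reference |
|---|---|---|---|---|---|---|---|---|
| 7 | 20% | 0–20% | 54–73% | 21 | 17.5 | 7 | 7 | 3.0 |
| 7 | 5% | 0–20% | 42–81% | 14–17.5 | 7 | 7 | 7 | 2.0–2.5 |
| 14 | 20% | 0–20% | 43–63% | 21–24.5 | 17.5 | 14 | 10.5 | 2.0–2.3 |
| 14 | 5% | 0–20% | 26–68% | 17.5–21 | 14 | 10.5 | 10.5 | 1.7–2.0 |
| 14 | 5% | 40% | 13% | 14 | 14 | 10.5 | 10.5 | 1.33 |
| 28 | 5–20% | 0–20% | 15–51% | 24.5–28 | 21–24.5 | 21 | 21 | 1.17–1.33 |
| 28 | 2% | 20–40% | 3–7% | 21 | 21 | 21 | 21 | 1.0 |
| 7 | 2% | 40% | 12% | 7 | 7 | 7 | 7 | 1.0 |

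Medians fall on a 3.5-day grid and cannot exceed 28 days. The reference keeps two other features of the rule: it drops people who cleared before the first convalescent stool, and it cuts off at week 4. The ratios therefore isolate the effect of new acquisitions.

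At 20% prevalence and 7-day carriage, requiring a positive diarrheal stool moves the median only from 21 to 17.5 days. The rest comes from reinfection after clearance.

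**The case against.** **The article is condensed, and convalescent shedding presupposes an infection being recovered from.** Matching rules are often left to a fuller document. But this sentence gives the start, the end and the set of stools, and the series is tied to diarrhea rather than to a detected pathogen. It is a stated rule that gives a biased answer if followed. Even if a positive diarrheal stool is read into it, reinfections are still timed to the last positive.

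**The size depends on assumptions.** This stands. Only the 20% is in the article, and it belongs to a power calculation for index children, whereas the series covers all household members. With 7-day carriage it implies 0.20 × 365/7, about 10 infections per person-year with one pathogen. A reader might take 3-fold, or 1.7- to 3-fold, as the general size; the table shows ratios down to 1.0.

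**The final positive can be a defensible endpoint.** This stands in part. If shedding is intermittent or a stool is missed, a late positive may be the same infection, and stopping at two negatives would shorten it wrongly. The described qPCR works at species level and cannot separate the two. This argument is much weaker for a first positive after a negative diarrheal stool.

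**Two stronger readings are not supported.** A reader might infer that the rule hides incident infections. The household model is meant to capture PCR-confirmed incidence observed in the study, and nothing says late positives are removed from it. A reader might also infer a known shift in the person-to-person versus environmental split. Duration only helps to parameterize two parameters, the priors for the relative importance of the routes come from the estimated relative risks, and no calculation here carries the bias through to the split.

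**Conclusion.** The point holds as a biased estimator. As written, infections acquired after onset, and reinfections after clearance, are counted as shedding from onset. The bias is upward relative to the same estimator without new acquisitions.

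Its size cannot be taken from the article. Under a two-state model with perfect detection and continuous carriage, it runs from no change in the median to about 3-fold (21 against 7 days). It is largest when prevalence is high and carriage short. It is small or absent when carriage is long, or when prevalence is low and many episodes are caused by the pathogen.

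The consequence that can be claimed is an inflated input to two transmission-model parameters. The effect on the model's conclusions is not known. The sentence should be changed because the remedy uses stools already planned for collection and testing.

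**What to change.** In Data analysis, change the shedding-duration sentence as follows:

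1. Estimate duration only from episodes whose diarrheal stool is qPCR-positive for the same target (*Shigella*, or the same *Campylobacter* species).
2. Do not count a first positive after a negative diarrheal stool as convalescent shedding.
3. For positives that follow negatives, report duration ended at the first of two consecutive negative stools alongside the final-positive version, as a sensitivity analysis. The gap between them shows how much depends on reading late positives as reinfection or as intermittent shedding.

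**Cost.** Only the analysis wording changes; no new sampling or testing is needed. Fewer episodes contribute, so the estimate is less precise. The two-negatives version may truncate some genuine intermittent shedding. It may also leave some upward bias (14 against 10.5 days at 14-day carriage and 20% prevalence in the table).

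### The shedding-duration rule ignores censoring and drops episodes with no positive convalescent stool, so it can misstate duration and levels off at about 28 days if shedding lasts longer

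*Protocol article*

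**What the plan says.** Under Human stools, the protocol article sets up a dedicated series whose purpose is given as "To characterize duration of pathogen carriage". Stools from anyone with diarrhea "will continue to be collected approximately twice-weekly for 4 weeks from illness onset, with a collection window of 48 hours". Separately, "Stool samples will be collected upon enrollment, monthly thereafter, and at the time of diarrhea", so there is a stool at onset, and routine monthly stools continue after the series ends. The text does not say whether those monthly stools count as convalescent.

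Data analysis then fixes the estimator of convalescent shedding as the "median time from the onset of symptoms to the final positive convalescent stool performed on all qPCR-positive convalescent stool samples". It states no handling for episodes still positive at the last stool or for episodes with no positive convalescent stool.

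The transmission-modeling part of the same section gives the use: "Prevalence and duration of shedding in convalescent stools will help to parameterize two model parameters". These two are a shedding rate and a factor that converts human shedding into environmental contamination.

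**The concern.** This is a stated rule, not a detail left to a fuller plan, and three faults follow from its wording.

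- **Right-censoring.** A person still positive at the final stool has an unknown, longer duration. The rule enters the date of that stool as the end of shedding.
- **Interval-censoring.** Clearance is known only to lie between the last positive and the next negative stool. The rule always uses the earlier date.
- **Selection on the outcome.** An episode positive at onset whose convalescent stools are all negative has no final positive convalescent stool, so it contributes nothing. These are the fastest clearers.

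The first two faults shorten the estimate and the third lengthens it. The net error therefore depends on the quantity being measured and need not be the same for the two organisms. The modeling is meant to place those organisms on a person-to-person versus environmental continuum, with shedding duration as one input.

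**Working it through.** The article reports no shedding-duration figure, so there is none to reproduce. The check applies the stated rule to assumed true durations.

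**Inputs from the article (Human stools).** Twice weekly is taken as every 3.5 days. Four weeks gives 28 / 3.5 = 8 stools, at days 3.5, 7, ..., 28. The 48-hour window can move the last stool to about day 30.

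**Assumptions.** Detection is perfect while shedding lasts. True duration is not in the article, so its median m is varied from 2 to 60 days. The main case is exponential; Weibull (shape 2) and lognormal (log-SD 0.8) are alternatives.

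**Formulas, exponential case.** P(T ≥ t) = 2^(−t/m).

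- Share of episodes dropped (no positive convalescent stool): 1 − 2^(−3.5/m).
- Among those kept, P(last positive ≥ t) = 2^(−(t − 3.5)/m). The reported median is the largest stool day at which this is at least 0.5.
- Share of kept episodes still positive at day 28: 2^(−24.5/m).

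| True median (days) | Reported median (days) | Dropped | Kept and still positive at day 28 |
|---|---|---|---|
| 2 | 3.5 | 70% | 0% |
| 5 | 7.0 | 38% | 3% |
| 7 | 7.0 or 10.5 (tie) | 29% | 9% |
| 10 | 10.5 | 22% | 18% |
| 14 | 14.0 or 17.5 (tie) | 16% | 30% |
| 28 | 28.0 | 8% | 55% |
| 40 | 28.0 | 6% | 65% |
| 60 | 28.0 | 4% | 75% |

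Simulation of 200,000 episodes per scenario agrees. The ties are exact. At m = 7, P(T ≥ 10.5 given T ≥ 3.5) = 2^(−7/7) = 0.5, so the result falls on either side by chance. With 0 to 2 days of random collection delay, the simulated values were 10.5 for a true 7, 17.5 for 14, 28.2 for 28 and 28.5 for 42.

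**Up to about 28 days.** In these exponential scenarios the error runs from 0 to about +3.5 days, or one sampling interval. Weibull durations simulated at 3.5, 7, 14, 21 and 28 days showed no error, but those values all sit on the sampling grid. Between grid points a less dispersed distribution can err downward. For Weibull with m = 24, P(T ≥ 24.5 given T ≥ 3.5) = 2^(−[(24.5/24)² − (3.5/24)²]) = 2^(−1.021) = 0.493. That is below 0.5, so 21 is reported, 3 days low.

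**Above about 28 days.** The estimate no longer moves: (28 − 40)/40 = −30%, (28 − 42)/42 = −33%, (28 − 60)/60 = −53%. Lognormal with true median 40 also gives 28.0, and Weibull with true median 42 gives 28.

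**Check of the remedy.** An exponential fit kept all episodes, placed those with no positive convalescent stool in the interval 0 to 3.5 days, and right-censored at day 28. Assumed medians of 3.5, 7, 14, 21, 28, 42 and 60 days came back as 3.5, 7.0, 14.0, 21.0, 27.9, 42.1 and 59.9. The fitted model was the true one, and values beyond 28 days are extrapolation.

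**The case against.** The strongest reply is that the rule works tolerably over much of the plausible range. A cap does not move a median while fewer than half of the retained episodes are positive at the last stool, and below about 28 days the error is at most about one sampling interval. That stands. So does the point that the article gives no durations, so neither organism is known to lie in the range where the estimate levels off.

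A second reply is that the target is convalescent shedding, for which conditioning on a positive convalescent stool is natural, and that prevalence of convalescent shedding is also used and can carry the early clearers. This has some force. The article does not, however, say how prevalence and duration would be combined, and prevalence does nothing for right-censoring.

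Third, shedding duration does not enter the relative risks or attributable fractions for the pathways. That is correct and limits the severity.

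Two stronger readings are tempting. A reader might infer that the model will take the reciprocal of the median as a clearance rate, and so calculate a rate error. The article never states that conversion. It says only that these inputs help to set the parameters, and part of any such error would come from swapping a median for a mean, which fully observed data would share. A reader might also infer a hard ceiling of 28 days. The collection window allows about 30, and later monthly stools are not expressly excluded.

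**Conclusion.** The point holds as a weakness of the stated estimator that should be fixed. The rule ignores right- and interval-censoring and, on its plain reading, omits episodes with no positive convalescent stool. Its error cannot be signed or sized from the article. Under the assumptions above (3.5-day spacing, perfect detection, assumed distributions) it is within about one sampling interval for true medians up to about 28 days. For longer shedding the estimate stays at about 28 days, so true medians of 40 and 60 days cannot be told apart.

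Distortion of the *Shigella* versus *Campylobacter* comparison is possible if either organism is shed for longer than about four weeks. It is not demonstrated, and the documents do not support saying that the transmission models will receive a wrong shedding rate.

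**What to change.** Replace the estimator in Data analysis as follows.

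- Include every diarrhea episode qPCR-positive for the organism at onset.
- Estimate duration by interval-censored survival analysis (Turnbull, or a parametric model), separately for *Shigella* and for each *Campylobacter* species analyzed.
- Treat an episode with no positive convalescent stool as cleared before the first convalescent stool. Right-censor an episode positive at its last stool.
- Pass the fitted distribution with its uncertainty to the transmission models, not a single median.
- State whether routine monthly stools count as convalescent. Use those taken after the series only in a sensitivity analysis: with an assumed infection prevalence of 20% (Sample size and power calculation), a later positive may be a reinfection.
- Flag any estimate beyond about 28 days as model-based extrapolation.

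The cost is revised wording, somewhat more analysis work and some dependence on the chosen model. No additional samples or visits are needed.
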